## Abstract

**Background:**

Knee osteoarthritis (OA) is a common, chronic, progressive and degenerative disease which affects patients’ quality of life and may cause disability and social isolation. OA is a huge economic burden for the patient and a large strain for the whole healthcare system. Articular cartilage has a small potential to repair, with progressively more clinicians emphasizing cellular therapy. Subcutaneous fat tissue in human body is a large reservoir of mesenchymal stem cells (MSCs) and is been harvested in minimally invasive, simple procedure. Up to date there is no prospective randomized controlled studies demonstrating effectiveness and role of adipose tissue injections in OA treatment. The purpose of this study is to assess functional and clinical changes among patients with symptomatic knee OA treated with intra-articular injections of autologous adipose tissue or platelet rich plasma (PRP) and to compare efficacy of both therapeutic methods.

**Methods:**

This is a prospective, randomized, controlled study. Patients who meet inclusion criteria will be allocated to Fat Tissue group or PRP group randomly. Subjects will receive an intra articular injection with autologous adipose tissue and PRP respectively. Patients will be assessed five times: before treatment and 1, 3, 6 and 12 months after the treatment. The assessment consists of patient reported outcome measures (The Knee injury and Osteoarthritis Outcome Score, International Knee Documentation Committee 2000, the Western Ontario and McMaster Universities Osteoarthritis Index, the Health Questionnaire EQ- 5D- 5 L), three functional tests (The Timed Up and Go Test, The 5 Times Sit to Stand Test, The 10 m Walk Test) and Maximal Isometric Voluntary Contraction.

**Discussion:**

This study protocol has several strengths and weaknesses. One of strongest point of this study is the wide, multidimensional functional assessment which will give a large amount of objective data. On the other hand, lack of blinding has to be considered as a risk of both subject and investigator bias.

**Trial registration:**

name of registry: ClinicalTrials.gov, trial registration number: NCT04321629, retrospectively registered on date of registration.

## Background

Knee osteoarthritis (OA) is a common, chronic, progressive and degenerative disease which causes irreversible structural changes, like cartilage loss, subchondral bone sclerosis and osteophyte formation. Those changes lead to clinical symptoms, such as joint stiffness, loss of function, crepitus, effusions and pain. This disease affects patients’ quality of life, and may cause disability and social isolation [1, 2]. Two types of OA exist, primary or idiopathic and secondary. Primary does not have a clear origin in contrast to the secondary, which is caused by known medical condition or trauma [3].

OA is a huge economic burden for the patient and a large strain for whole healthcare system [4, 5]. There are several treatment options for knee OA [1–3, 6, 7]. Guidelines have been published by organizations such as European League Against Rheumatism (EULAR) or the National Institute for Health and Clinical Excellence (NICE) [5]. The choice of an adequate method depends on given patients’ joint condition and symptoms intensity. Patient education, weight loss, aerobic and strength training are first line recommendations. Next stages include paracetamol, topical and oral non-steroidal anti-inflammatory drugs (NSAIDs) and a variety of options for symptom relief, like manual therapy, transcutaneous electrical nerve stimulation and other physical therapy methods. In some cases, when conservative treatment fail, more invasive treatment like arthroscopy, partial or total arthroplasty is needed [5].

Articular cartilage has a limited potential to repair, with progressively more clinicians emphasizing cellular therapy [8]. Platelet rich plasma (PRP) is a well-proven method in OA treatment [9–12]. Promising results have been found in OA treatment with Bone-Marrow Derived Stem Cells (BMSCs) [13], but it has been noticed that adipose tissue may be a better source of Mesenchymal Stem Cells (MSCs) [14]. Concentration level of MSCs is much higher in adipose tissue than in bone marrow (2% vs 0.02% respectively) [1]. Moreover, subcutaneous tissue in human body is a large reservoir of MSCs and is been harvested in minimally invasive, simple procedure.

Autologous subcutaneous fat tissue obtained by a lipoaspiration process is widely available at clinics, despite limited evidences of its effectiveness. Up to date there is no prospective randomized controlled studies demonstrating effectiveness and role of adipose tissue injections in OA treatment.

## Design

This is a prospective, randomized, controlled study. The purpose of this study is to assess functional and clinical changes among patients with symptomatic knee OA treated with intra-articular injections of autologous adipose tissue or PRP and to compare the efficacy of both therapeutic methods. We hypothesize that adipose tissue injections will improve patients’ quality of life and functional status and will decrease pain level significantly more than PRP injections. In addition to the functional tests and muscle strength measurement, the patient reported outcome measures (PROMs) of the knee joint function and quality of life will be used to assess each participant.

The study design meets CONSORT, MIBO and SPIRIT guidelines.

### Inclusion and exclusion criteria

All activities related with the study will be performed at the Department of Spine Disorders and Pediatric Orthopedic Surgery, Poznan University of Medical Sciences and Rehasport Clinic in Poznan, Poland. These include patient identification, explanation of all procedures, treatment and functional assessment. The same inclusion criteria have been established for an Experimental Group (subjects treated with autologous fat tissue) and a Control Group (subjects treated with PRP). Those criteria consist of: symptomatic knee OA, age between 45 and 65 y.o., Kellgren- Lawrence grades I – III OA, no or minimal positive effects of previous conservative treatment (rehabilitation, hyaluronic acid injections, steroid injections), VAS pain level minimum 4 in one knee, VAS pain < 2 in the contralateral knee. Those patients who meet inclusion criteria will be allocated to Fat Tissue Group or PRP Group randomly (Fig. 1). The exclusion criteria were as follows: use of local corticosteroids up to 3 months or hyaluronic acid injections up to 6 months prior to the study, past or present joint infection, previous knee arthroscopy surgery up to 1 year prior to examination, peripheral inflammatory diseases (rheumatoid arthritis, spondyloarthropathies, etc.), total arthroplasty and osteotomy, ankylosis of the joint, dermatitis or dermatological disease at the intended injection site, coexistence of degenerative changes in other limb joints (hip, foot), cancer, oral corticosteroid therapy, use of medicines that affect blood clotting, pregnancy or breast-feeding. Before randomization, patients will sign a suitable consent form. All participants will be obliged not to use any anti-inflammatory drugs for the entire duration of the study. Moreover, every volunteer will receive a brochure approved by Research and Development Department which contains all of the information regarding protocol (procedures, outcomes assessments, schedule of visits, researchers team, possible complications). Draw is made at the Doctor’s room after subject’s qualification and the participant choose the number of the group 1 or 2, Fat Tissue Treatment or PRP treatment, respectively. At the stage of treatment there is no possibility for patients to be blinded because the procedure requires adipose tissue harvesting. However, during all other stages, the procedure will be blinded, in a database each participant will have a special code to minimize the risk of identification as well as reporter biases.

**Fig. 1 Fig1:**
[figure not shown]
Study design

### Lipoaspiration procedure

Lipoaspiration will take place in the operating room under general anesthesia for patient’s and doctor’s comfort. The most frequent donor site is abdomen [14, 15]. The patient will be placed in a supine position. At first, two small incisions at the level of umbilicus will be made by the trained orthopaedic surgeon (TP or PB). Then Klein solution (saline with lidocaine and epinephrine) will be infused to reduce bleeding. Ten minutes is required for infiltration. Next step is a liposuction performed with a thin cannula inserted through incisions. Finally, skin sutures and the pressure dressing will be applied. To minimize risk of bleeding and hematoma, an elastic belt will be recommended, as well as partial weight bearing within first 2 weeks. Harvested adipose tissue will be prepared in a Lipogems kit [14]. The final product will be transferred into 10-ml syringes. About 10 ml of the product will be injected into the affected knee joint. After several hours of observation, the patient will leave the clinic with 2 elbow crutches. For the first 2 weeks, partial weight-bearing will be allowed as tolerated. After 2 weeks, full-weight loading will be allowed. Patients will be instructed to perform physical exercises, including cycling, swimming and full-body exercises. No physical therapy will be recommended.

### PRP procedure

PRP preparation takes place in an outpatient clinic. The whole process, from blood collection to PRP injection, takes approximately 10 min. It takes places in the treatment room at room temperature and day light exposure. No commercial kit are used. 10-ml sterile collecting tubes containing citrate will be placed in a centrifuge (Centrifuge MPW- 223e) with a tilting rotor. Rotation will last 7 min at 2320 * g. After centrifugation, PRP will be collected up to 3 ml for separate 10-ml syringe. 3 ml of PRP will be injected into the knee joint. Procedure will be repeated three times in 7 day interval.

### Injection procedure

Joint injection will be performed by TP or PB in the same manner for both groups: patient placed in supine position, affected knee extended, a 21-Gauge needle inserted into the suprapatellar pouch, in case of joint effusion – aspiration of synovial fluid and finally administration of autologous fat tissue or PRP.

For the first 2 weeks after injections patients will be asked to limit their activity. 2 weeks after the third injection, normal activity will be allowed. Patients will be instructed to perform physical exercises, including cycling, swimming and full-body exercises. No physical therapy will be recommended.

### Outcomes measurement

Patients will be assessed five times: before treatment and 1, 3, 6 and 12 months after the treatment (Table 1). The PROMs consist of the four questionnaires: The Knee injury and Osteoarthritis Outcome Score (KOOS) [16–18], International Knee Documentation Commitee 2000 (IKDC 2000) [19, 20], the Western Ontario and McMaster Universities Osteoarthritis Index (WOMAC) [21, 22], the Health Questionnaire EQ- 5D- 5 L [23, 24].

**Table 1 Tab1:** The study procedures schedule

Visit	1	2	3	4	5
Month (m)	0	1 m	3 m	6 m	12 m
Study qualification	X				
Consent form signing	X				
Autologous fat tissue/ PRP intra- articular injection	X				
Questionnaires:					
KOOS	X	X	X	X	X
IKDC 2000	X	X	X	X	X
WOMAC	X	X	X	X	X
EQ-5D-5 L	X	X	X	X	X
Functional tests:					
TUG	X	X	X	X	X
5xSTS	X	X	X	X	X
10mWT	X	X	X	X	X
Strength measurement:					
MVIC	X	X	X	X	X

Moreover, three functional tests will be performed to assess patient’s functional status: The Timed Up and Go Test (TUG) [25], The 5 Times Sit to Stand Test (5xSTS) [26], The 10 m Walk Test (10mWT) [27]. To assess strength parameters of the knee flexors and extensors the Maximal Voluntary Isometric Contraction (MVIC) will be measured. Each test will be supervised by the same one physiotherapist to avoid any interexaminer bias and discrepancies during testing.

### PROMs

The Knee injury and Osteoarthritis Outcome Score is currently culturally adapted in 39 languages, including polish [18, 28]. The polish version has already been validated [17]. It is used for knee OA assessment and for the evaluation of the effect of many orthopedic surgeries as well [16].

International Knee Documentation Committee 2000 has been developed to assess function, symptoms and sports activity in patients with variety of knee joint conditions such as: OA, meniscal and/or ligamentous injuries, patellofemoral pain [19]. This questionnaire also has been adapted to the polish language [20].

The Western Ontario and McMaster Universities Osteoarthritis Index has been developed for knee and/or hip joints OA symptoms assessment. This questionnaire has been extensively tested for reliability and validity in measuring changes in patients’ symptoms in affected joints [21, 22]. There is no polish cultural adaptation of WOMAC that is why WOMAC index will be calculated from KOOS [29].

The Health questionnaire EQ- 5D- 5 L measures general health status including function, physical symptoms and emotional dimensions which are relevant even for healthy individuals. EQ- 5D- 5 L is 5- level, more sensitive version of the original 3- level version (EQ- 5D- 3 L) [24]. Polish population norms for the EQ- 5D- 5 L has already been established [23].

### The functional tests

#### The timed up and go test

The Patient sits on a standard chair (45 cm height) and is asked to stand up and walk straight on in a comfortable pace to the line (placed on the floor 3 m from the chair), turn around and go back to the starting position. The result of this test is time measured with stopwatch. Time limit for this test is 3 min 30 s. If the patients fails, the reason should be recorded. The participant is allowed to use the crutches or a walker if needed [25].

#### The 5 times sit to stand test

The Patient sits on a standard chair (45 cm height) without back support with arms crossed on a chest and is asked to stand up (fully extend hips and knees) then sit down again and repeat it five times. The participant starts on the rater’s command and the rater counts loudly each repetition. The result of this test is time measured with stopwatch. The stopwatch is stopped when the subject sits down after the fifth repetition. The patient is not allowed to bounce from the chair and use any other support [26].

#### The 10 m walk test

The patient stand in upright position and is asked to walk straight on, as fast as he/she can to the line marked on the floor 10 m from the starting point. The participant starts on the rater’s command. The result of this test is time measured with stopwatch. The patient is not allowed to run but may use the crutches or a walker if needed [27].

### Maximal voluntary isometric contraction measurement

MVIC measurement is performed with Forcemeter FB 500 (AXIS, Gdansk, Poland). The patient sits on a bench with the belt around waist and legs placed freely beyond the table. The measuring belt is placed parallel to the floor just above the ankle joint with knee flexed to 90 degrees. The measuring belt length is strictly specified: for MVIC of extensors 160 cm, for MVIC of flexors 60 cm.

The procedure starts with the measuring belt pretension, then the patient is asked to extend/flex the knee as hard as he/she can and hold it for 6 s. The force is measured in Newtons [N]. The results is divided by the patient’s weight [kg] for data analysis.

### Ethics, data management and statistical analysis

All procedures used for this study have been approved by Bioethics Committee, Poznan University of Medical Sciences on 16th December 2019 (no. 868/18). The tile of the project accepted by Bioethics Committee: “Prospective functional evaluation of knee osteoarthritis treatment with autologous fragmented adipose tissue and platelet-rich plasma (PRP) – comparison of two different treatment methods”. All patients will be obliged to give written agreement for the participation in the study. Collected data will be stored at the clinic in a database created particularly for this study containing appropriate security features. In database each participant will have a special code to minimize the risk of identification of a given patient. Only patients who attended all of visits, performed each functional test and MVIC and fulfilled each questionnaire will be included in the analysis. The consequence of the absence on a visit will be exclusion from the study. Basic analysis will include descriptive statistics of demographic characteristics to assess both groups homogeneity. Such analysis will be done several times during testing to detect any confounders which may influence the balance between treatment groups. At the start we consider BMI, age, sex and knee OA grade as a possible confounders, but in a further analysis we will also look for any correlations between them and treatment effectiveness. At every time point the results will be compared between treatment and control group, what is main purpose of this study. The results obtained in each questionnaire, functional test and MVIC will create the effect across all time points. A *p*- value of < 0.05 will be considered statistically significant.

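### The analysis is restricted to patients with every visit, test and questionnaire complete, and a missed visit ends participation, so the randomised comparison becomes completers-only: less precise and open to bias

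*Protocol article*

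**What the plan says.** Under Ethics, data management and statistical analysis, the protocol article defines the analysis set: "Only patients who attended all of visits, performed each functional test and MVIC and fulfilled each questionnaire will be included in the analysis". The next sentence is a rule of conduct: "The consequence of the absence on a visit will be exclusion from the study". The two differ in reach. A missed visit ends participation, while a missed test or questionnaire removes the patient only from the analysis.

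The same section sets the main comparison: "At every time point the results will be compared between treatment and control group, what is main purpose of this study". Allocation is random (Inclusion and exclusion criteria: "Those patients who meet inclusion criteria will be allocated to Fat Tissue Group or PRP Group randomly"). The schedule under Outcomes measurement is: "Patients will be assessed five times: before treatment and 1, 3, 6 and 12 months after the treatment". Each visit has four questionnaires, three functional tests and the MVIC, but under PROMs the "WOMAC index will be calculated from KOOS", so seven instruments are collected separately. For the timed up and go test the article foresees failure: "If the patients fails, the reason should be recorded".

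The article mentions no all-randomised analysis set, missing-data method or sensitivity analysis that would offset the rule. The Discussion names lack of blinding and small size as limitations, but not this restriction.

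**The concern.** Random allocation makes the two groups comparable at entry. The rule then selects patients on events after randomisation, which has three consequences.

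- **Every time point is conditioned on the whole year.** A patient with complete data at 1, 3 and 6 months who misses month 12 drops out of the earlier comparisons too.
- **Endpoints are tied together.** One missing EQ-5D-5L removes the same patient's KOOS, walking times and strength at all visits.
- **Data go uncollected.** After one absence the patient leaves the study, so later visits are lost. No later analysis plan can recover them.

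The article itself gives reasons why loss could differ by arm. Patients know their treatment (Inclusion and exclusion criteria). The fat-tissue arm has general anaesthesia, liposuction and crutches (Lipoaspiration procedure). The PRP arm has three short outpatient injections a week apart (PRP procedure). The Discussion accepts that the fat procedure is harder on patients and that early contact differs. On a plain reading, a patient unable to perform a test could also be removed, and that inability is itself information about outcome.

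At stake is the decision described in the Discussion: the fat procedure is to be adopted only on a definite, significant and clinically noticeable difference. In a trial that calls itself small, a modest selection effect bears on that.

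**Working it through.** The article gives no sample size, power, SD or dropout rate, so there is no figure to reproduce. All rates below are assumptions.

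**Inputs from the article.** Four post-treatment visits and five assessments in all. Seven separately collected instruments (KOOS, IKDC, EQ-5D-5L, TUG, 5xSTS, 10mWT, MVIC), so 7 × 5 = 35 required measurements. Significance level 0.05, taken as two-sided.

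**1. Retention.** With independent misses, the share kept is (1 − m)^4 for a per-visit miss rate m, multiplied by (1 − q)^35 for a per-measurement miss rate q.

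- m = 5%: 0.95^4 = 0.815, about 81%.
- m = 10%: 0.90^4 = 0.656, about 66%.
- m = 5% and q = 0.5%: 0.8145 × 0.995^35 = 0.8145 × 0.839 = 0.683, about 68%. Counting only the 28 post-baseline measurements gives 0.8145 × 0.995^28 = 0.708, about 71%.

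If patients who miss one visit were kept in follow-up, any single visit would have 95% or 90% of patients at m = 5% or 10%. The rule brings this down to 81% or 66%.

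**2. Power, for an assumed reference trial.** With d = 0.5 SD and 80% power, n per arm = 2(1.96 + 0.842)² / 0.5² = 62.8, so 63. Power = Φ(d√(n/2) − 1.96).

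| Completers | n per arm analysed | Power | Randomised per arm to hold 80% |
|---|---|---|---|
| 100% | 63 | 80.1% | 63 |
| 80% | 50.4 | 70.9% | 63/0.8 → 79 |
| 70% | 44.1 | 65.1% | 63/0.7 = 90 |

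Not all of this loss is due to the rule, since a missing 12-month value is missing under any analysis. The rule adds the discarded values that were observed or could have been.

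**3. Bias with no true difference.** Simulation with 50 randomised per arm, correlation 0.7 between the 6- and 12-month results, and a completers-only comparison at 12 months. Where dropout depends on outcome, its log-odds rise as the 6-month result worsens, by 0.5 to 1.5 per SD in the third row and 1.0 to 1.5 in the second.

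| Assumed mechanism | Spurious difference | Type I error |
|---|---|---|
| Loss unrelated to outcome, or equal loss by the same mechanism | about 0 | about 5% |
| Same mechanism in both arms, 22% to 25% loss (fat) vs 12% (PRP) | about 0.06 to 0.09 SD | about 6% to 7% |
| Only fat-arm loss depends on outcome; PRP loss random at 12% | about 0.07 to 0.20 SD | about 6% to 15% |

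A separate calculation lets missingness depend directly on the outcome analysed, with the same slope in both arms (0.5 to 1.0 per SD). Loss of 20% vs 10% gives 0.05 to 0.08 SD and type I error of 5.5% to 6.7%. Loss of 30% vs 10% gives 0.09 to 0.16 SD and 7.0% to 11.1%.

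In all these scenarios poor results go missing more often, so the error favours the arm with more loss.

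**The case against.** The rule is explicit and nothing in the article offsets it. The strongest objections concern how far the consequences can be pushed, and most of them stand.

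- **Bias is not shown.** A reader might infer that the result will be biased towards fat tissue. The article gives no dropout data. With no true difference, between-arm bias needs loss that relates to outcome and differs by arm in amount or mechanism; otherwise only precision suffers. The direction is also open: unblinded PRP patients who are disappointed could be the ones who leave.
- **The largest figures need a one-sided assumption.** The upper range, to 0.20 SD, requires PRP loss to be random while fat-arm loss is not. Nothing in the article supports that asymmetry.
- **Deletion of the worst outcomes is inference.** The article asks for the reason when a patient fails the TUG. It does not say that a failed attempt counts as not performed. The TUG allows 3 min 30 s and walking aids, and the 10 m walk also allows aids, so failure may be uncommon in patients aged 45 to 65 with grade I–III disease.
- **Harms and surgery.** A reader might infer that complications will be under-reported or that conversions to surgery vanish. The rule concerns the analysis set and attendance; the article says neither.
- **Guidelines.** The claim that "The study design meets CONSORT, MIBO and SPIRIT guidelines" is not used here, because the content of those guidelines is not in the document.
- **A mixed model is no guarantee.** It removes bias when missingness depends on observed data. Loss for unrecorded reasons may not follow that pattern.

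What survives is enough: a stated rule discards valid randomised data, stops collection after one absence and allows selection between arms.

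**Conclusion.** The concern holds as a badly fixed analysis rule, and it needs correcting. Loss of precision is certain as soon as any patient has incomplete data. Bias is a risk of unknown size and direction. On the assumed rates, 66% to 81% of patients remain if 5% to 10% miss each follow-up visit, and 68% if 5% per visit is combined with 0.5% per measurement. With no true difference and 50 per arm, the spurious effect lies between 0 and about 0.20 SD, and about 0.06 to 0.09 SD when both arms share one mechanism but lose 22% to 25% versus 12%. These figures rest on assumed dropout rates, slopes, correlation and sample size; none comes from the article. That the trial will give a wrong answer does not follow from the document.

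**What to change.** Delete both sentences and replace them with rules to this effect:

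1. A patient who misses a visit, test or questionnaire stays in the study, and later visits are still collected unless consent is withdrawn.
2. All randomised patients are analysed in their allocated arm, using all available data for each endpoint separately. One suitable model is a mixed model for repeated measures with baseline value, arm, visit and arm × visit.
3. One sensitivity analysis addresses data not missing at random.
4. A test that could not be performed because of the knee is recorded as such and handled in a separate rank-based or composite sensitivity analysis. A worst rank cannot enter a mixed model on times or forces.
5. Losses and their reasons are reported by arm for all randomised patients.
6. The completers analysis is kept only as a sensitivity analysis.

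The first rule is the urgent one: the Discussion says recruitment has begun, and uncollected visits cannot be restored later. The cost is continued contact with patients who miss a visit, slightly more analysis work, and a missing-at-random assumption in the main analysis. No extra patients are needed.

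### Group balance is to be re-examined repeatedly to find confounders, while the baseline score and the four named factors have no fixed role in the arm comparison

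*Protocol article*

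**What the plan says.** All of the analysis text stands in the protocol article under 'Ethics, data management and statistical analysis'.

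- **Balance check.** "Basic analysis will include descriptive statistics of demographic characteristics to assess both groups homogeneity". The next sentence makes this a repeated exercise with a stated aim: "Such analysis will be done several times during testing to detect any confounders which may influence the balance between treatment groups". The number of looks, their timing and what follows from them are not given.
- **Named factors.** "At the start we consider BMI, age, sex and knee OA grade as a possible confounders". Their only stated use is that "in a further analysis we will also look for any correlations between them and treatment effectiveness".
- **Arm comparison.** "At every time point the results will be compared between treatment and control group, what is main purpose of this study". The threshold is stated once: "value of < 0.05 will be considered statistically significant". One further sentence mentions an effect built up over all visits, without a model that can be identified.
- **Analysed set.** Only patients with every visit, test and questionnaire are analysed, and a missed visit removes the patient from the study.

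Under 'Outcomes measurement', "Patients will be assessed five times: before treatment and 1, 3, 6 and 12 months after the treatment". Table 1 lists every outcome at month 0, so a baseline value is scheduled for each patient. The allocation draw under 'Inclusion and exclusion criteria' describes no stratification by the four factors. The Discussion calls the study small; no sample size is given.

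**The concern.** In a properly randomised trial, the full randomised set can differ at baseline only by chance. A search for confounders by repeated inspection of the arms therefore has little to find except chance differences, and each one found invites a decision taken after data have been seen. The plan has already identified four plausible prognostic factors and collects the strongest usual candidate, the baseline value of each outcome. It could fix their role now, but it leaves that role open.

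Two things are at stake. The first is that the adjusted analysis, if there is to be one, is undefined in advance. The second is precision: a comparison that ignores the baseline score discards information already collected and stays exposed to chance baseline differences. Both weigh more in a small study.

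**Working it through.** The article gives no sample size, effect size, standard deviation or correlation, so there is no figure of its own to reproduce. Its inputs are the 0.05 threshold, the four named factors and the five assessments. Everything else below is an assumption.

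**1. Precision from baseline adjustment.** Let rho be the correlation between baseline and follow-up score. The variance of the adjusted arm difference is 1 - rho² times that of a follow-up-only comparison, and (1 + rho)/2 times that of a change-score comparison.

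| rho (assumed) | 1 - rho² | Saving vs follow-up only | (1 + rho)/2 | Saving vs change score |
|---|---|---|---|---|
| 0.4 | 0.84 | 16% | 0.70 | 30% |
| 0.5 | 0.75 | 25% | 0.75 | 25% |
| 0.6 | 0.64 | 36% | 0.80 | 20% |

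Against follow-up only, the savings equal 1/0.84 = 1.19, 1/0.75 = 1.33 and 1/0.64 = 1.56 times the patients. For scale, an assumed effect of 0.5 SD with 80% power at two-sided 0.05 needs 63 per arm unadjusted and 48 per arm adjusted at rho = 0.5.

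**2. Exposure to chance imbalance.** If the arms differ by an assumed 0.3 SD on the baseline score, an unadjusted follow-up comparison shifts by 0.3 × rho: 0.12, 0.15 and 0.18 SD at rho = 0.4, 0.5 and 0.6.

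**3. Type I error under three ways of handling covariates.** Null simulation with 3,000 runs at each of 20, 30 and 50 per arm. Outcome variance is 1, baseline correlation 0.5, and there are four independent normal factors with coefficient 0.2 each.

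| Approach | Type I error |
|---|---|
| Baseline score and four factors fixed in advance | 0.045-0.050 |
| Factors added because they looked imbalanced at any of three looks | 0.041-0.045 |
| Smallest p-value over all 16 subsets of the four factors | 0.09-0.11 |

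Only the third approach inflates the error.

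**4. Chance flags, conditional only.** If each of four independent factors were formally tested at 5%, at least one would be flagged in 1 - 0.95⁴ = 0.185 of sound trials at one look. With three equally spaced looks during enrolment, the rate per factor is about 0.107, giving 1 - 0.893⁴ = 0.364 (0.35-0.39 in the simulation). The article mentions neither formal tests nor three looks. If the looks fall after enrolment ends, the same patients give the same baseline picture apart from dropout, and the rate stays near 19%.

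**The case against.** The strongest reply is that the text speaks of descriptive statistics and never says that a flagged factor enters a model. A reader might infer data-driven covariate selection and hence unreliable p-values, but the article does not state that step. Even if it were taken, selection on imbalance alone does not inflate type I error (step 3). The inflated figure needs selection on the result. Looking at the factors against effectiveness leaves that route open, but open is all it is. This part of the reply stands.

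Second, the analysed set is completers only, in a trial without blinding. Imbalance there need not be chance, because dropout may differ by arm, and rechecking the remaining patients could then have a legitimate purpose. This also stands: the chance argument covers all randomised patients and not the completers. Rechecking would reveal such loss but would not repair it.

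Third, the article does not say whether raw or change scores are compared, and the Design section words its aim in terms of change. Absence of stated adjustment is not proof that baseline is ignored, and model form is commonly left to a full protocol or SAP. This is correct, and silence on the model alone would not be a point. What remains is a stated procedure, repeated looks to detect confounders, which a later plan would have to override.

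A reader might also infer that interim balance tables could steer later allocation. The article does not say that the looks happen while enrolment is open, or that those who run the draw would see them. That inference is not supported.

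**Conclusion.** The point holds as a poor stated method, not as a demonstrated bias. The repeated homogeneity analysis has no stated number, timing or consequence. The four named factors have no role beyond later correlations, and the main comparison has no stated adjustment for the baseline score. The consequences are an adjusted analysis left open until data are seen and, if baseline is indeed unused, a variance that adjustment would cut by 16-36%. If change scores are meant, the cut is 30-20%. Both ranges rest on an assumed rho of 0.4-0.6.

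The type I error of about 0.09-0.11 applies only if covariates are chosen by their effect on the result. The chance-flag rate of about 36% applies only to formal 5% tests at three looks during accrual. Neither is a property of the plan as written. The change should be made, but it is a correction of wording and not a threat to the design.

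**What to change.** 1. Replace the repeated homogeneity analysis with one descriptive table of baseline characteristics for all randomised patients.
2. Add a separate descriptive table of completers against non-completers by arm, because the completers-only rule can create imbalance that is not chance.
3. For each outcome, fix one model in advance: arm, visit, arm-by-visit interaction, baseline value of that outcome, BMI, age, sex and OA grade. Keep these terms whatever balance is observed.
4. Label the correlations of the four factors with effectiveness as exploratory.

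All of these variables are either named as factors already or scheduled in Table 1, so the cost is analysis wording and a few degrees of freedom. The degrees of freedom deserve a check against the actual sample size, since the study is described as small. The change does not resolve multiplicity across visits and outcomes, which needs its own rule on which contrast is primary.
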